If vitamin D between 81 and 100 ng/ml • Start or continue taking cod liver oil and multivitamin • Reduce total vitamin D intake by 50% ∘ The goal is half the dosage from all sources participant was taking at the time the blood measurement was made ∘ If the vitamin D_3_ supplement dosage was in fractions; then, round it down to the next available pill in the market. ∘ E.g., if the total taken is 7000; 1000 from MV, 1000 from calcium/vitamin D_3_ supplement and 5000 IU vitamin D_3_ we want to halve the dose; then the total amount to take becomes 3500. We will ask the participant to continue calcium/vitamin D_3_ (1000 IU), switch to our MV (1000 IU), start cod liver oil (400 IU), which totals 2400. The remaining vitamin D_3_ (3500–2400) is 1100 IU (round down to 1000 IU), so we prescribe a 1000-IU pill once daily. • Send letter to participant and primary care/neurologist	
If vitamin D 40 to 80 ng/ml At visits 2, 3, and 4: • Start or continue taking cod liver oil and multivitamin which contain about 1400 IU between the two supplements. Keep participant on current dose of vitamin D if in this range. At all visits: • Do not change vitamin D dose. E.g., if the participant is taking 4000 IU from their personal physician, participant should stay on that dose. If they were taking 5000 IU from their personal physician they should stay on that dose. If participant is taking more than 5000 IU or less than 4000 IU, participant should continue on that dose. • No need to start vitamin D_3_ supplement if not on any.	

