If vitamin D value less than 40 ng/ml but more than 20 ng/ml If visit 1 blood result: • Wait until visit 2. At visit 2: • If not taking any vitamin D, begin 5000 IU daily. Participant will also begin or continue taking cod liver oil and multivitamin according to the supplement schedule. • If taking 4000 IU vitamin D_3_ or less daily, participant will be instructed to increase vitamin D_3_ to 5000 IU and add or continue taking cod liver and multivitamin according to the supplement schedule. • If the participant is already taking 5000 IU but does not take the supplement regularly (i.e., daily) they will be instructed to take the supplement every day and add or continue taking cod liver oil and multivitamin. • If taking 5000 IU or more they should add or continue taking cod liver oil and multivitamin. Discuss with [name] for further guidance on the appropriate vitamin D dose.^a^ The patient and primary care/neurology team will be notified by letter of the lab results and the vitamin D, cod liver oil and multivitamin recommendations. • Send letter to participant and primary care/neurologist if participant is instructed to change vitamin D intake prescribed by medical personnel If visit 2 blood result: • Wait until visit 3 blood result. If visit 3 or 4 blood result: • And participant is taking 5000 IU vitamin D, cod liver oil and the multivitamin, discuss with [name] for further guidance.^a^ An increase in the vitamin D dose will likely be recommended by [name] and personalized results letters will be sent separately to the participant and their primary care/neurology team.	

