If vitamin D value 20 ng/ ml or less If visit 1 or 2 blood result: • Refer participant back to primary care physician and neurologist, recommending the primary care physician or neurologist prescribe vitamin D_2_ 50,000 IU once per week until vitamin D level is greater than 40 ng/ml. Alternatively, the primary care physician may recommend 6000 to 10,000 IU vitamin D_3_ daily if preferred over vitamin D_2_. • Send letter to participant and primary care/neurologist • Call and notify participant that vitamin D level is severely low and advise them that a letter is being sent to them and their primary care/neurology team. *If visit 2, 3, or 4* • Call participant to clarify if the participant is taking any vitamin D supplements, cod liver oil or multivitamin and discuss with [name] for further guidance. If already on vitamin D_3_ 5000 IU or a vitamin D_2_ supplement per their local medical team, the participant may continue the vitamin D until they see their primary care/neurology team for further guidance. Continue or add cod liver oil and multivitamin as scheduled. • Send letter to participant and primary care/neurologist	

^a^The total vitamin D_3_ from vitamin D_3_ supplement (including cod liver oil and the multivitamin) recommended by the study team should not exceed 7000 IU/d (cod liver oil and multivitamin have approximately 1400 IU daily combined) unless approved specifically by [name].

Abbreviation: *MV* Multivitamin

**Table 3 Tab3:** Outcomes: change after 12-week intervention and 12 weeks of sustained intervention relative to observation period

Primary outcome measure:	
1. Perceived fatigue assessed by FSS.	
Secondary outcome measures:	
1. Perceived fatigue assessed by MFIS;	
2. Perceived fatigue assessed by FSMCF;	
3. Gait speed assessed by T25FW;	
4. Distance walked assessed by 6MWT;	
5. Speed of task completion in 9HPT;	
6. Number of correct responses assessed by SDMT-O;	
7. Quality of life as measured by MSQOL-54;	
8. Quality of life as measured by SF-36;	
9. MSISv2 score;	
10. Anxiety and depression as measured by HADS;	
11. Physical activity (average daily steps and average minutes spent sedentary, light intensity physical activity, moderate intensity physical activity and vigorous intensity physical activity) and sleep (total sleep time, sleep efficiency) as measured by the accelerometer;	
12. Sleep quality as measured by PSQI;	
13. Stress as measured by PSS-10;	
14. Physical activity as assessed by IPAQ-L;	

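### Table 2 recommends ending the weekly vitamin D2 course above 40 ng/ml, but its 40 to 80 ng/ml row tells staff to keep that dose unchanged

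*Protocol article*

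**What the plan says.** Under Dietary supplements, the protocol article sets vitamin D by the blood level at visit 1 and later visits, with a target range of 40 to 80 ng/ml. Table 2 gives the rule for each band of values. Two bands matter here.

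- **20 ng/ml or less, visit 1 or 2 result.** Staff are to "Refer participant back to primary care physician and neurologist, recommending the primary care physician or neurologist prescribe vitamin D_2" at "50,000 IU once per week until vitamin D level is greater than 40 ng/ml". The same entry offers another option: "Alternatively, the primary care physician may recommend 6000 to 10,000 IU vitamin D_3_ daily if preferred over vitamin D_2". No end level is written for that option.
- **40 to 80 ng/ml.** For visits 2, 3 and 4: "Keep participant on current dose of vitamin D if in this range". Whatever the visit, the rule is: "Do not change vitamin D dose. E.g., if the participant is taking 4000 IU from their personal physician, participant should stay on that dose". The row then extends this to doses outside its examples: "If participant is taking more than 5000 IU or less than 4000 IU, participant should continue on that dose".

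Footnote a, which is marked in the 20 to 40 ng/ml row, limits the vitamin D3 that the study team recommends to 7000 IU per day unless specifically approved.

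**The concern.** The weekly course is meant to lift a very low level. If it works, the participant's next study value falls in the 40 to 80 ng/ml row. At that point one row says the course has reached its end and the other says the dose stays as it is. This is a clash between two printed rules, and it arises in the trial's own visit sequence.

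Two staff members who apply the table in good faith could handle the same participant differently until the next study value, about 12 weeks later. That bears on participant safety and on uniform delivery of a supplement regimen given in both arms. Serum vitamin D and calcium are also among the blood biomarkers listed as secondary outcomes in Table 3.

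**Working it through.** The plan states no figure to reproduce. The check sets the rows side by side, with one conversion.

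**Inputs (Table 2 and its footnote; visit schedule).** Weekly D2 course: 50,000 IU, with an end level of more than 40 ng/ml. Upper branch of the 40 to 80 row: more than 5000 IU. Footnote limit: 7000 IU per day of study-recommended D3. Visits 2, 3 and 4: weeks 12, 24 and 36.

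**Step 1: does the course fall in the upper branch of the 40 to 80 row?** The doses in the table's D3 rules are daily amounts, so the weekly dose is converted: 50,000 / 7 = 7,142.9, or about 7,143 IU per day. This exceeds 5000 IU, so the sentence on continuing applies.

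**Step 2: where do the rows disagree?** Take a participant who starts the course after a visit 1 or 2 value of 20 ng/ml or less and is still on it at the next study visit.

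| Next study value | 20-or-less row, on the D2 course | 40 to 80 row |
|---|---|---|
| Exactly 40 ng/ml | End level not yet passed; continue | Keep the dose |
| Above 40, up to 80 ng/ml | End level passed; course ends | Keep the dose |

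The rows agree at exactly 40 ng/ml and disagree over the rest of the target range.

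**Step 3: does the text elsewhere settle it?**

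- *Prescriber.* The 40 to 80 row cannot be confined to doses set by the study, because its own examples are doses from the personal physician.
- *Footnote a.* It concerns vitamin D3 recommended by the study team, so it does not reach a D2 course prescribed by an outside physician.
- *Referral or notice.* The 20 to 40 row and the 20-or-less row both contain a step to discuss the case with a named person, and every band except 40 to 80 includes a letter to the treating team (conditional in part of the 20 to 40 row). The 40 to 80 row has neither. When the end level is crossed, Table 2 gives staff a keep-the-dose instruction and no step to tell the prescriber.

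**Step 4: timing.** Visits 2 and 3 are 24 − 12 = 12 weeks apart, as are visits 3 and 4 (36 − 24 = 12). A difference in handling at one visit could therefore last about 12 weeks before the next study value.

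**The case against.** The strongest reply is that the two rows speak to different people. The 20-or-less row advises an outside physician. The 40 to 80 row instructs study staff and can be read as telling them not to interfere with an outside prescription, which then ends on its own written term. On that reading, ending the course is part of the prescription and not a change to it. It is true that the stop is only a recommendation, and a reader who inferred two directly opposed study orders would go too far. But Table 2 does not state the harmonising reading, and the sentence on doses above 5000 IU tells the participant to continue without exception.

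Other limits stand in full:

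- **Not everyone in the lowest band.** A reader might infer that every participant who responds meets the conflict. The D3 alternative has no written end level to contradict. On D2, the physician may also have ended the course before the study visit.
- **The 20 to 40 row.** A reader might see a second contradiction for someone at 21 to 39 ng/ml at visit 1, told at visit 2 to start or raise vitamin D3, whose visit 2 blood is then in range. That row says a visit 1 result is acted on at visit 2, and the texts agree if the current dose is the one just ordered. No laboratory turnaround time is given to show otherwise.
- **Size.** One could multiply 12 weekly doses by 50,000 IU to get 600,000 IU between two visits. That is an upper bound, reached only if the course runs on for all 12 weeks.
- **An article condenses.** This does not answer the point: Table 2 is printed band by band with worked examples, and the printed rules themselves disagree.

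**Conclusion.** The point holds in a narrow form. For a participant still on the weekly D2 course at a study visit, with a value above 40 and up to 80 ng/ml, Table 2 contains both a recommended stop and a staff instruction to continue, and nothing printed says which governs. The conclusion rests on the text alone and on the conversion to about 7,143 IU per day.

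The number affected cannot be derived: the documents give no distribution of vitamin D levels, no split between the D2 and D3 options, and no duration of the course in practice.

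The conflict has no bearing on power or the primary analysis. Table 1 lists the same supplements for both arms and Table 2 adjusts vitamin D by blood level and not by assigned diet, so a reader who inferred bias between the diets would have no support in the documents. What is at stake is consistent and safe handling of a supplement course.

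**What to change.** Reconcile the 20-or-less row and the 40 to 80 row of Table 2 so that there is one instruction for a participant who reaches 40 to 80 ng/ml while on a course begun under the 20-or-less row. The same wording should say whether the prescriber is to be notified of that value. Which instruction should prevail is for the sponsor and its clinicians; no dose or rule is proposed here.

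The cost is a wording change in Table 2 and in any staff instructions drawn from it. No new measurement, visit or analysis is needed.

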A modified version of the Paleolithic diet was shown to reduce perceived fatigue in pwPMS (either secondary or primary progressive multiple sclerosis [SPMS or PPMS, respectively]) [4, 5] as part of a multimodal intervention (modified Paleolithic diet, targeted vitamin supplementation, stress-reducing practices, exercise, and electrical muscle stimulation). The study diet stressed the consumption of more vegetables, with a target of 6 to 9 cups of vegetables and fruit per day, and recommended somewhat less meat than Paleolithic diets tested in the previously mentioned studies. At enrollment, study participants were consuming less than 1.5 servings of vegetables per day but raised this to an average of 8 servings per day by month 12 [5]. The dietary component of the multimodal intervention was significantly associated with favorable changes in mood and cognition between baseline and 12 months, whereas the nondietary components were not [25]. It is unknown whether the dietary component of the multimodal intervention also significantly contributed to the observed reduction in perceived fatigue [4, 5]; however, several participants anecdotally reported that deviations from the study diet resulted in a sharp worsening of their fatigue and noted that the fatigue resolved with stricter adherence to the study diet. Data from another pilot randomized controlled trial also showed significant reductions in perceived fatigue (as assessed by FSS) in individuals with relapsing-remitting multiple sclerosis (RRMS) following a modified Paleolithic diet intervention [35].

To establish the specific effects of diet on MS symptoms such as fatigue, this study focuses on diet only instead of the previously tested multimodal intervention. The modified Paleolithic diet continues to stress a high intake of vegetables but also eliminates foods to which some individuals may be sensitive: eggs and nightshade vegetables [29]. To enhance adherence and reduce the rate of dropout, which occurred early in the intervention among participants in a nondiet control group [35], control participants will be assigned a second diet, a low saturated fat (Swank) diet, which is also popular among the MS community and has research to support its efficacy.

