Supplements	• 1 tsp. cod liver oil • 1000 μg methyl B_12_ • 1000 μg methylfolate • 5000 IU vitamin D_3_^a^ • 1 multivitamin/mineral tablet for men aged 50+ without iron	• 1 tsp. cod liver oil • 1000 μg methyl B_12_ • 1000 μg methylfolate • 5000 IU vitamin D_3_^a^ • 1 multivitamin/mineral tablet for men aged 50+ without iron

^a^Dose adjusted based on serum vitamin D

##### Study diet 1

The modified Paleolithic diet stresses more vegetables than other Paleolithic diets that have been studied previously, and it limits meat to 6–12 oz per day. Like other Paleolithic diets, it excludes all grain, legumes, and dairy (except for clarified butter or ghee) and additionally excludes eggs. Nightshade vegetables/spices will be excluded during the first 12 weeks on the diet and then reintroduced during the second 12 weeks on the diet, if the participant desires, to safely test tolerance to nightshades while under study team observation. Specific guidance will be provided to participants about how to reintroduce nightshades into the diet.

##### Study diet 2

The low saturated fat diet restricts saturated fat to ≤ 15 g per day and limits unsaturated fat to 20–50 g (4–10 teaspoons) per day. (This diet is promoted by the Swank MS Foundation [38] and includes more emphasis on vegetables and whole grains than the original Swank Diet.)

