#### Dietary supplements

All study participants will follow the supplement regimen outlined in Table 1, with the exception of vitamin D_3_ (amount prescribed will vary on the basis of vitamin D level measured in the blood at visit 1 and subsequent visits as outlined in Table 2; target range, 40–80 ng/ml). After review of participant’s dietary supplement intake, study staff will ask participants to discontinue over-the-counter dietary supplements containing the study supplement ingredients (fish oil, vitamin D, vitamin B_12_, folate, and/or multivitamins) and use study supplements instead. Participants will be instructed to continue taking all other dietary supplements they have been using and not to begin any new supplements until after study completion. If the participant is asked to discontinue a supplement recommended by their physician or neurologist, the research team will send a letter to the treating physician, detailing which supplements have been discontinued and which supplements have been initiated as part of the study protocol.

**Table 2 Tab2:** Vitamin D dosing based on blood level

If vitamin D > 100 ng/ml and elevated calcium (Ca^2+^) > 10.2 mg/dl • Call study participant and have them stop vitamin D immediately, increase water intake. a. If Ca^2+^ level was 10.2–10.5: call your local physician, or urgent care for guidance. b. If Ca^2+^ level was 10.6 or higher: go to the emergency room for evaluation and probable intravenous fluids. • Stop or do not start taking the cod liver oil or the multivitamin • When vitamin D < 80 ng/ml, resume vitamin D at a reduced dose and cod liver oil and multivitamin per local primary care or neurology guidance • Call and notify the study participant’s primary care/neurology team about the high vitamin D level • Send letter to participant and primary care/neurologist	
If vitamin D > 100 ng/ml and normal calcium Ca^2+^ 8.5–10.2 mg/dl • Study staff will call the participant and have them stop all vitamin D supplements. Participant will follow up with their primary care doctor or neurologist. • Stop or do not start taking cod liver oil but may continue multivitamin • When vitamin D < 80 ng/ml, may resume vitamin D at a reduced dose and cod liver oil and multivitamin per local primary care or neurology guidance • Call and notify the study participant’s primary care/neurology team about the high vitamin D level • Send letter to participant and primary care/neurologist	

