15. Cognitive performance as measured by PDQ;	
16. Change in mood as measured by the MHI.	
17. Nutritional adequacy of the diet as measured by food frequency questionnaire (FFQ) and food records;	
18. Changes in blood biomarkers (insulin, glucose, hemoglobin A1c, lipids including HDL, vitamin K, vitamin D, calcium, vitamin B_12_, folate, homocysteine, complete blood count with differential, Cardio IQ® [fatty acid levels]).	

*Abbreviations: 6MWT* 6-Minute walk test, *9HPT* 9-hole Pegboard Test, *Cardio IQ®* Omega-3 (EPA + DHA) Index, Omega-6/Omega-3 Ratio, EPA/Arachidonic Acid Ratio, Arachidonic Acid, EPA, and DHA, *DHA* Docosahexaenoic acid, *EPA* Eicosapentaenoic acid, *FFQ* Food Frequency Questionnaire, *FSMCF* Fatigue Scale for Motor and Cognitive Function, *FSS* Fatigue Severity Scale, *HADS* Hospital Anxiety and Depression Scale, *HDL* High Density Lipoprotein, *IPAQ-L* International Physical Activity Questionnaire–Long, *MFIS* Modified Fatigue Impact Scale, *MHI* Mental Health Inventory, *MSIS v2* Multiple Sclerosis Impact Scale version 2, *MSQ* Medical Symptoms Questionnaire, *MSQOL54* Multiple Sclerosis Quality of Life 54, *PDQ* Perceived Deficits Questionnaire, *PSQI* Pittsburgh Sleep Quality Index, *PSS 10* Perceived Stress Scale 10, *SDMT-O* Symbol Digit Modalities Test-Oral, *SF-36* 36-item Short Form Health Survey, *SPMSQ* Short Portable Mental Status Questionnaire, *T25FW* Timed 25-foot Walk

Study staff will provide participants with a list of supplements to purchase and will reimburse participants for all study supplements. Participants will be instructed to begin supplements on the 11th day of the diet to allow them time to purchase the supplements after returning home from visit 2. They will introduce one new supplement every third day to allow time to identify any potential adverse reactions. If side effects are noted, the participant will be told to stop the supplement and contact study staff.

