Both study groups are likely to experience reductions in MS-related symptoms. Differences within and between groups will be assessed for clinical significance, supported by statistical analyses. Because the primary outcome measure is a self-reported measure and not an objectively measured laboratory or imaging result, the NMSS requested two modifications in the study design. First, a 12-week observation period was added, during which participants continue to eat their usual diet, so that each participant can be her or his own control in the repeated-measures analyses. Second, an accelerometer measure was added to the study to provide an objective assessment of the change in physical activity, sleep duration, and sleep quality.

Given the anecdotal reports regarding improvement in MS symptoms with dietary changes, results from this study will contribute to understanding of the optimal dietary approach for reducing MS-related fatigue. Findings of the study as well as any challenges observed will be submitted to journals for publication. Published papers will be listed on the [name] website ([name]).

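### Both arms start a study supplement regimen soon after the diet, so the within-arm changes in hypotheses 1a and 1b cannot be credited to diet alone

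*Protocol article*

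**What the plan says.** The Background gives the purpose in a sentence that ends by contrasting this trial with the earlier multi-part package: "To establish the specific effects of diet on MS symptoms such as fatigue, this study focuses on diet only instead of the previously tested multimodal". The same section lists the parts of the earlier package and counts supplementation separately from the diet: "multimodal intervention (modified Paleolithic diet, targeted vitamin supplementation, stress-reducing practices, exercise, and electrical muscle stimulation".

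The Supplements row of Table 1 is identical for the two diets: "1 tsp. cod liver oil • 1000 μg methyl B_12_ • 1000 μg methylfolate • 5000 IU vitamin D_3_^a^ • 1 multivitamin/mineral tablet". The Dietary supplements section applies it to all participants. Only the vitamin D3 amount varies, following Table 2, with a target range of 40–80 ng/ml. On timing it says: "Participants will be instructed to begin supplements on the 11th day of the diet to allow them time to purchase the supplements". One new product is then added every third day. Overlapping products that participants already use are replaced: "study staff will ask participants to discontinue over-the-counter dietary supplements containing the study supplement ingredients".

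Under Study Design, the observation period is described only as usual diet. The Discussion says it was added "so that each participant can be her or his own control in the repeated-measures analyses". Hypotheses 1a and 1b are stated within each arm against that period. Hypothesis 3 asks whether the 12-week changes persist at 24 weeks. Hypotheses 2a to 2c compare the arms.

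**The concern.** The Background treats supplementation as one of the things bundled with diet in the earlier work and says this trial looks at diet by itself. The supplements are nevertheless kept, and their start falls on the intervention side of the before-and-after contrast. Dietitian coaching also begins at visit 2. Within an arm, a fall in the Fatigue Severity Scale (FSS) therefore has at least three candidate causes that switch on almost together.

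This matters because the Discussion expects both groups to improve. If both do, and the arms differ little, the natural reading is that both diets work, when part of the change could come from what the arms share. Hypothesis 1b is the most exposed. It predicts no significant change on the low saturated fat diet, and a shared supplement effect could overturn that prediction or enlarge the change predicted on the other diet.

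A lesser matter is the biomarker outcome in Table 3, item 18: "Changes in blood biomarkers (insulin, glucose, hemoglobin A1c, lipids including HDL, vitamin K, vitamin D, calcium" and others. Several of its analytes are nutrients that the regimen supplies directly.

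**Working it through.** **1. Timing on the full schedule.** Inputs from Dietary supplements: start on day 11, one product every third day, five products. The intervention period is 12 × 7 = 84 days.

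- Start days: 11, 14, 17, 20, 23.
- Days on at least one product: 84 − 11 + 1 = 74, and 74/84 = 88%.
- Days on all five: 84 − 23 + 1 = 62, and 62/84 = 74%.
- Follow-up: the regimen continues throughout.

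These are properties of the full schedule, not of every participant (see the objection).

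**2. Can any FSS score show diet without supplements?** The Measures section says FSS is collected every 4 weeks. The exact schedule is in Fig. 2, which is not shown. Assuming the count runs from visit 2, the first on-diet score falls near day 28, after the last scheduled start on day 23. No primary-outcome score would then reflect diet alone. The mixed models under Data analysis could separate diet from supplements within an arm only through non-randomized differences between participants in prior use and vitamin D3 start.

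**3. How sensitive is the within-arm test?** Inputs from Table 4, FSS row, within groups: difference 1.2–2.0, SD 1.1–1.4, correlation 0.6, n = 34, alpha 0.05 (two-sided assumed).

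- SD of change = SD × √(2(1 − 0.6)): 1.1 × 0.894 = 0.984, and 1.4 × 0.894 = 1.252.
- The plan's figure first: in the least favourable case, 1.2 / (1.252/√34) = 5.59, and the paired t test has power 0.9997. This is consistent with the stated within-group power of at least 0.85.
- Change detectable with 80% power: (1.960 + 0.842) × 0.984/√34 = 0.47, and (1.960 + 0.842) × 1.252/√34 = 0.60.

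So a supplement effect of 0.47–0.60 FSS points, with no diet effect at all, would have 80% power to give a significant within-arm change. The documents give no supplement effect on FSS, so the following values are assumptions that show the range:

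| Assumed supplement-only FSS change | Power, SD 1.4 | Power, SD 1.1 |
|---|---|---|
| 0.3 | 27% | 41% |
| 0.5 | 62% | 82% |
| 0.7 | 89% | 98% |

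**4. Which hypotheses are affected?**

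| Hypothesis | Contrast | Supplements differ across the contrast? |
|---|---|---|
| 1a, 1b | Intervention against observation, within arm | Yes, on the study regimen |
| 3 | 24 against 12 weeks on diet | No, in use at both times; it inherits the 1a/1b changes |
| 2a–2c | Randomized arms | Same regimen in both arms |

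**The case against.** The strongest reply is that the supplements are disclosed as part of the intervention. They sit in a table headed as the study diets, and the section describing them is under Intervention. The Abstract and the opening of the Background describe the earlier package without mentioning supplements. The Abstract also ties the diet-only focus to the comparison of two diets, which is the contrast that survives. This makes the problem smaller but does not remove it. The passage that names the components counts supplementation apart from diet, and hypotheses 1a and 1b speak of the diet intervention while setting each arm against a period without the study regimen.

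Several objections to stronger readings stand:

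- **Exposure varies.** Some participants already take overlapping products, so the study product is a substitution for them. Under Table 2, vitamin D3 is not started in those at 40–80 ng/ml who take none, and a very low visit 1 level prompts referral during observation. The 88% and 74% should not be read as every participant's exposure.
- **Table 3.** A reader might infer that its heading credits the diet. It refers to the intervention and needs no change.
- **Hypothesis 3.** A reader might treat it as equally confounded. Its own claim is persistence, with supplements in use at both times.
- **Biomarkers.** Homocysteine is not a supplied nutrient and should not be listed as one. A common regimen leaves the between-arm biomarker comparison valid, so reclassifying these outcomes is not required.
- **Other pre-post limits.** Entry requires FSS of at least 4, so regression to the mean and expectation of benefit remain. Relabelling the within-arm change makes its description accurate but does not make it a clean causal estimate.

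**Conclusion.** The point holds for within-arm attribution. Changes in hypotheses 1a and 1b against the observation period reflect the study diet, the study supplements and coaching together, and the documents describe no period or arm that separates them. Severity is moderate. No sample size, dose, schedule or primary contrast changes.

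A reader might go further and infer that the between-diet fatigue comparison is compromised. The documents do not support that: the regimen is the same in both arms and participants are randomized, so 2a to 2c estimate the diet difference on a common supplement background. Nor do the documents show that supplements affect FSS. The figures of 0.47–0.60 say only how large such an effect would need to be for 80% power, given Table 4's SDs and correlation, 34 per group and a two-sided 5% test.

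For the directly supplied nutrients (vitamin D, B12, folate, EPA/DHA), within-arm change mainly reflects supplementation. For vitamin D, adjusting the dose to a target range also tends to narrow any difference in level between arms.

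**What to change.** 1. State hypotheses 1a and 1b as change on the study intervention, defined as study diet plus study supplements with coaching. Note that hypothesis 3 inherits this definition.
2. Drop diet-specific attribution from within-arm results, and reserve diet-specific conclusions for the between-arm contrast in 2a to 2c.
3. Interpret within-arm changes in vitamin D, B12, folate and EPA/DHA as mainly reflecting supplementation. Report vitamin D intake by arm beside the blood level, because the adjusted dose may carry a difference that the level hides.

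The cost is wording plus one table. Participants already record supplements with their food records around each visit, and vitamin D prescribing is driven by study visits, so no new data collection should be needed. With the article published and recruitment under way, the wording can go into the analysis plan and the results report. The price is a narrower within-arm claim.
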